##### 2.5..2..2. Sleep impairment.

The multifactorial nature of chronic pruritus requires comprehensive diagnostic procedures and lengthy therapies. It is important to treat visible scratch lesions and accompanying disorders, including sleep disorders. The Epworth Sleepiness Scale is a scale developed for determining sleep impairment.^[12]^ The measurement will be performed at baseline (visit 1), 2 weeks, and 4 weeks during and after treatment (visits 2 and 3) and at follow-up after 4 weeks (visit 4) for both groups.

##### 2.5.2.3. Molecular analysis.

Investigating changes in serum cytokine levels may help us understand the mechanism of action of *Sopoongsan* in patients with chronic pruritus. The serum levels of pruritus-related cytokines such as IFN-γ, IL-4, immunoglobulin E (IgE), and TSLP will be analyzed.^3^ The assessment will be conducted at baseline (visit 0) and 4 weeks after treatment (visit 3) for both groups. Blood collected from patients in both groups will be immediately centrifuged at a temperature below 4°C. The obtained plasma and serum samples will be stored at a temperature below −80°C until further analysis. The samples will be analyzed by Global Clinical Central Laboratories (Republic of Korea).

##### 2.5.2.4. Feasibility.

The feasibility of the recruitment process will be measured for conducting a large-scale RCT. The proportion of the number of participants who have been recruited, screened, met the inclusion criteria, agreed to participate, and dropped out will be used to calculate.

### 2.6. Safety assessment and adverse events

A clinical laboratory examination will be performed at baseline, before drug administration, and at 4 weeks after completing drug administrations (visit 3), as a safety assessment for all participants. The liver and renal function can possibly be affected by herbal medicines^[13]^; therefore, liver and renal function tests will be performed additionally, as well as serum potassium concentration assessment because *Glycyrrhiza radix*, a component of *Sopoongsan*, can induce hypokalemia.^[14]^ All adverse events, which are undesirable and/or unexpected medical findings that were absent before commencing this clinical trial, will be recorded. The IRB at Kyung Hee University will be reported, and they will determine whether the trial should be discontinued. The causal link between the adverse events and the procedure will be categorized into six stages. Appropriate treatment and follow-up will be provided for severe adverse events.

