### 2.2. Participant recruitment

A total of 20 participants with upper body pruritus will be recruited through posters placed in the hospital and community, local newspapers, and subway advertisements from November 2022 to December 2023. The participants who meet the eligibility criteria (Table 1) will receive information regarding the clinical study during a consultation with the coordinator and provide written informed consent for their participation in this study. Subsequently, all participations will be randomly allocated to either the treatment or control group.

**Table 1 T1:** Patient eligibility criteria.

Inclusion criteria
(1) Patients aged ≥ 19 years (2) NRS score of ≥ 3 for upper body pruritus (3) Pruritus of ≥ 3 months (4) Diagnosis: allergic atopic or seborrheic dermatitis (5) Provided voluntary written informed consent to participate in this clinical study
Exclusion criteria

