(1) NRS score of ≥ 7 for upper body pruritus (2) History of taking oral adrenal corticosteroids (steroids) or immunosuppressants for skin itching within the last 4 weeks (3) Skin diseases caused by bacterial or viral infections (4) Clinical abnormality of liver and renal function tests (i.e., ALT, AST, ALP) ≥ 2 times the upper limit of normal or creatinine > 2.0 mg/dL at screening (5) Severe acute cardiovascular disease (i.e., heart failure, myocardial infarction, stroke, hypertension, or diabetes) (6) Serious conditions of hyperlipidemia, anemia, active pulmonary tuberculosis, thyroid disease, and other infectious and systemic diseases (7) Past or present malignant tumors (8) Antipsychotic drug treatment within 2 months before screening test (9) History of acute or chronic pancreatitis or gastrointestinal surgery (except for simple appendix surgery or hernia surgery) (10) Genetic problems such as galactose intolerance, Lapp lactase deficiency, or glucose-galactose malabsorption (11) History of hypersensitivity reactions to the constituents of the clinical trial treatments (12) History of drug or alcohol abuse (13) Pregnant and lactating women or in case or accepting the implementation of an appropriate contraceptive method among women of pregnant potential who are likely to become pregnant (except for women who have undergone sterilization) (14) Plan to participate in other clinical trials after enrollment in this clinical trial, or who have participated in other clinical trials during the 30 days prior to registration in this clinical trial (15) Inappropriate patients as considered by the investigator for other reasons

ALP = alkaline phosphatase, ALT = alanine aminotransferase, AST = aspartate aminotransferase, NRS = numeric rating scale.

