### 2.7. Statistical methods

#### 2.7.1. Sample size.

This study will be an exploratory clinical trial to determine the degree of symptomatic improvement that can be achieved with *Sopoongsan* treatment in patients with upper body chronic pruritus. However, statistical hypotheses and effect sizes for the estimation of the sample size cannot be established. Therefore, as a pilot study based on research feasibility, this study considers a total of 20 subjects, 10 per group.

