#### 2.7.2. Statistical analysis.

All statistical analyses will be conducted using SAS® version 9.4 (SAS Institute, Inc., Cary, NC). The *p*-values will be two-sided and set at 5% level of significance. A complete set analysis will be conducted to analyze the effectiveness of the intervention, and a per-protocol analysis will be additionally verified. Missing data will be analyzed using the last observation carried forward imputation method. For efficacy analysis, the mixed-effect model for repeated measures will be used, with each group and visit time as fixed factors and subjects as random factors. Student’s paired *t* test will be used to compare the factors before and after treatment. All adverse events (including severe adverse events) will be classified by group.

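### The adverse event definition covers only findings absent before the trial, so worsening of dermatitis, itch or an already abnormal laboratory value need not be recorded as an adverse event

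*Protocol article*

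**What the plan says.** The definition is given in Section 2.6, which has all adverse events recorded and describes them as "undesirable and/or unexpected medical findings that were absent before commencing this clinical trial". The same section provides for reporting to the IRB, which decides whether the trial should stop, and for grading the causal link in six categories. It also says that "liver and renal function tests will be performed additionally, as well as serum potassium concentration assessment", because herbal medicines may affect the liver and kidneys and one ingredient may lower potassium.

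The planned safety analysis in Section 2.7.2 is one sentence: "All adverse events (including severe adverse events) will be classified by group".

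Table 1 in Section 2.2 describes who enters. Inclusion requires "NRS score of ≥ 3 for upper body pruritus (3) Pruritus of ≥ 3 months (4) Diagnosis: allergic atopic or seborrheic dermatitis", and exclusion criterion 1 removes those with "NRS score of ≥ 7 for upper body pruritus". Exclusion criterion 4 removes participants with ALT, AST or ALP "≥ 2 times the upper limit of normal or creatinine > 2.0 mg/dL at screening". Table 1 has no potassium criterion.

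**The concern.** The usual test for an adverse event is whether something untoward appears or gets worse after treatment starts. Section 2.6 keeps only the first half of that test. In a trial where everyone already has a skin disease with itch, the missing half covers worsening of the treated condition itself. It also covers deterioration of a laboratory value that was already out of range, in the organ systems that the section singles out for extra testing.

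The label matters because other steps depend on it. Recording, causality grading, reporting to the IRB, stopping the intervention because of adverse events (Section 2.4) and the classification by group (Section 2.7.2) all refer to adverse events. Something that is not recorded as one can miss each of these steps, even if a related number sits elsewhere in the data. If two assessors read the clause differently, like events will also be recorded inconsistently.

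**Working it through.** No figure in the plan has to be reproduced. The check sets the definition beside the sections that use it and the criteria that decide what is present at baseline.

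**1. Is the definition widened anywhere?** Four other places use the term or a close relative.
- Section 2.4 lists adverse events among the reasons for discontinuation.
- Table 2 schedules identification of adverse reactions at visits 2, 3 and 4.
- Section 2.7.2 classifies adverse events by group.
- Section 2.8 has an independent committee look at safety and investigate adverse events.

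None of them redefines the term or mentions an increase in severity or frequency. Section 2.6 is the only definition in the article.

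**2. What is present at baseline in every participant?** Itch of NRS 3 or more, pruritus for at least 3 months, and atopic or seborrheic dermatitis. The exclusion at 7 puts entry scores from 3 to below 7 on a scale that ends at 10 (Section 2.5.1). Assuming whole-number scores, entry is 3 to 6, and the room to worsen is 10 − 6 = 4 points to 10 − 3 = 7 points. Nobody is so close to the top of the scale that worsening is impossible. Since itch and dermatitis are present at entry by design, an increase in either is not clearly a finding that was absent before.

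**3. What may be present at baseline in some participants?** Criterion 4 admits ALT, AST or ALP above normal but below 2 times the upper limit, and creatinine up to 2.0 mg/dL. Whether a given creatinine in that range counts as abnormal depends on the laboratory's reference range, which the article does not give. No named criterion bars a low potassium at entry. How many participants will have any such value is not stated, and it could be none.

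**4. What is captured regardless of the definition?**

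| Worsening of | Other record in the schedule (Table 2, Section 2.6) | What is still at risk |
|---|---|---|
| Itch | NRS at screening and visits 1 to 4 | Adverse event label, causality grade, IRB route, by-group count |
| Liver, renal or potassium value | Laboratory tests at baseline and visit 3 | The same |
| Dermatitis lesions | No lesion-severity score; DLQI (visits 1 to 4) and concomitant drug changes (visits 1 to 3) reflect a flare only indirectly | The same, and also the direct record of the flare |

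The gap is therefore widest for a dermatitis flare and narrower for itch and laboratory values, where the numbers survive but need not enter the safety process.

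**5. Can the size be computed?** The plan is that "this study considers a total of 20 subjects, 10 per group", so 20 of 20 participants have a condition whose worsening the definition does not clearly cover. That is a count of people, not of lost events. The article gives no flare rate and no expected proportion with abnormal laboratory values, so no number of missed events follows.

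**The case against.** Four arguments stand against the point.

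*The clause speaks of findings, not conditions.* An enzyme at 5 times the upper limit in someone who entered at 1.9 times could be called a finding absent at baseline, and so could a lesion at a new site. This stands in part. A reader might infer that such a rise certainly fails to qualify, but the wording does not settle that. It leaves the matter to the assessor, which is itself a defect in a definition.

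*This is a condensed article.* The full protocol, version 1.3, is not shown and may be worded differently. That is possible. But the article does not leave the matter open: it states a criterion, and the criterion is incomplete. If version 1.3 already covers worsening, the two texts need reconciling.

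*Worsening is measured anyway.* This is largely true for itch and laboratory values, and it limits the impact. It is not true for skin lesions, and the scheduled measurements do not by themselves lead to causality grading or IRB reporting.

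*The consequence is easily overstated.* This stands in full. A reader might infer that Sopoongsan would look safer than it is, or that the events lost are the most likely ones in this population. The documents support neither. The definition applies to both blinded arms. If the drug reduces itch, uncounted flares would fall more on placebo, and the distortion would run the other way. Any laboratory abnormality that arises from a normal baseline meets the definition as it stands.

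A reader might also treat the absence of an analysis set for treated participants as part of this problem. It is not: that belongs in a statistical analysis plan, which is not shown.

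**Conclusion.** The point holds as a defect in a stated definition. As written, Section 2.6 does not require worsening of a pre-existing condition to be recorded as an adverse event. This touches the dermatitis and pruritus of all 20 planned participants, and those liver or renal values that are abnormal at entry but allowed by criterion 4. Such events could then miss causality grading, IRB reporting and the by-group classification.

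The size of the effect is unknown. Neither the number of events lost nor the direction of any between-group distortion can be determined from the documents. The conclusion rests on two assumptions: that assessors follow the clause as written, and that the full protocol does not widen it. It should be corrected because the gap concerns safety recording and is easy to close, not because a bias in favour of either arm has been shown.

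**What to change.** Replace the clause in Section 2.6 with a definition along these lines: an adverse event is any untoward medical finding that is new, or that worsens in severity or frequency, after the first dose of study medication, whether or not it is considered related. State expressly that this includes worsening of dermatitis or pruritus and of laboratory values that were abnormal at baseline. Put the same wording in the case report form instructions, so that assessors judge worsening against the recorded baseline. If version 1.3 of the protocol already says this, align the published text with it.

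No extra visit, test or participant is needed: the baseline values and the adverse event checks are already in Table 2. The cost is a short change of text and a few more events recorded in both arms. Some of these will be ordinary fluctuation of the underlying disease, which the planned six-category causality grading can take into account.

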### 2.7. Statistical methods

#### 2.7.1. Sample size.

This study will be an exploratory clinical trial to determine the degree of symptomatic improvement that can be achieved with *Sopoongsan* treatment in patients with upper body chronic pruritus. However, statistical hypotheses and effect sizes for the estimation of the sample size cannot be established. Therefore, as a pilot study based on research feasibility, this study considers a total of 20 subjects, 10 per group.

#### 2.7.2. Statistical analysis.

All statistical analyses will be conducted using SAS® version 9.4 (SAS Institute, Inc., Cary, NC). The *p*-values will be two-sided and set at 5% level of significance. A complete set analysis will be conducted to analyze the effectiveness of the intervention, and a per-protocol analysis will be additionally verified. Missing data will be analyzed using the last observation carried forward imputation method. For efficacy analysis, the mixed-effect model for repeated measures will be used, with each group and visit time as fixed factors and subjects as random factors. Student’s paired *t* test will be used to compare the factors before and after treatment. All adverse events (including severe adverse events) will be classified by group.

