## 2. Methods

### 2.1. Study design and setting

This clinical study will be a randomized placebo-controlled trial investigating the effectiveness of *Sopoongsan* in the treatment of upper body pruritus in patients with allergic atopic or seborrheic dermatitis. *Sopoongsan* or placebo will be administered orally three times daily for 4 weeks, with a follow-up of 4 weeks. A flow chart describing the clinical study design is illustrated in Figure 1. The effect of *Sopoongsan* on itching will be assessed by improvements in itching symptoms, Dermatology Life Quality Index, presence of sleep disorders due to itching, and changes in immune indicators in the blood. The study setting and site of data collection will be the Clinical Trial Center at the Kyung Hee Korean Medical Hospital, Kyung Hee University, in the Republic of Korea.

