### 2.5. Outcome measures

To evaluate the effect of *Sopoongsan* on skin itching, the intensity of pruritus, as assessed using a numeric rating scale (NRS), will be the primary outcome. The secondary outcome measures will include findings from instruments that evaluate the quality of life, sleep impairment, and changes in the immune response. The schedule for outcome measurements is illustrated in Table 2.

**Table 2 T2:** Schedule for enrollment, clinical outcomes, and safety assessment.

Period	Screening	Treatment			Follow-up*
Visit	Screening	Visit 1	Visit 2	Visit 3	Visit 4
Week	0 week (baseline)	1 week	2 weeks	4 weeks	8 weeks
Provide informed consent	**○**				
Identification of inclusion and exclusion criteria	**○**				
Demographics	**○**				
Medical and disease history	**○**				
Clinical laboratory examination	**○**			**○**	
Vital signs	**○**			**○**	
NRS	**○**	**○**	**○**	**○**	**○**
DLQI		**○**	**○**	**○**	**○**
ESS		**○**	**○**	**○**	**○**
Blood collection for immune analysis	**○**			**○**	
Supply of drug for clinical trial		**○**	**○**		
Medication compliance			**○**	**○**	**○**
Identification of adverse reaction(s)			**○**	**○**	**○**
Identification of concomitant drug change		**○**	**○**	**○**	

DLQI = Dermatological Life Quality Index, ESS = Epworth sleep scale, NRS = numeric rating scale.

* Follow-up by phone interviews.

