#### 2.5..1. Primary outcome: intensity of pruritus.

The NRS is a numerical rating scale anchored at 0 and 10 that is marked by patients to indicate their intensity of itch. It has been validated in large-scale studies for chronic pruritus.^[12]^ The intensity of pruritus, as assessed using the NRS, will be the primary outcome. The measurement will be performed at baseline (visit 1), 2 weeks, and 4 weeks during and after treatment (visits 2 and 3) and at follow-up after 4 weeks (visit 4) for both groups.

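### The stated NRS model yields one group difference averaged over visits, which on the natural reading includes the pre-dose baseline and so understates the end-of-treatment effect

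*Protocol article*

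**What the plan says.** Section 2.5.1 sets the endpoint: "The intensity of pruritus, as assessed using the NRS, will be the primary outcome". It names no primary time point. On timing it says "The measurement will be performed at baseline (visit 1), 2 weeks, and 4 weeks during and after treatment (visits 2 and 3"), and then "at follow-up after 4 weeks (visit 4) for both groups". Baseline is therefore numbered as a visit and listed with the later ones.

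Section 2.1 says that study drug "will be administered orally three times daily for 4 weeks, with a follow-up of 4 weeks", so the week-8 value is taken four weeks after dosing ends.

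For efficacy, section 2.7.2 says "the mixed-effect model for repeated measures will be used, with each group and visit time as fixed factors and subjects as random factors". It mentions no group-by-visit term, baseline covariate, change score or visit-specific contrast. It adds "Missing data will be analyzed using the last observation carried forward imputation method", and its p-"values will be two-sided and set at 5% level of significance". The only other efficacy test is a paired t test of before against after, which gives no between-group comparison.

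Table 2 does not match section 2.5.1. Its screening column is "0 week (baseline"), its visit 1 is at week 1, and NRS is marked at weeks 0, 1, 2, 4 and 8. DLQI and ESS are not marked at week 0, although sections 2.5.2.1 and 2.5.2.2 call visit 1 the baseline for both.

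**The concern.** A model with group and visit as main effects assumes the same group difference at every visit. If baseline is one of those visits, randomisation contradicts that assumption whenever the drug works, because the expected difference before dosing is zero. The fitted group term then blends a null visit, a partial-treatment visit, the end of treatment and an off-drug visit. It is not the effect of four weeks of treatment.

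This is the only between-group efficacy analysis that the article describes. Section 2.7.1 gives the aim as finding how much improvement the drug achieves, and the Discussion offers the study as a basis for large trials. A later trial sized on a diluted figure would be sized wrongly. With the SD held fixed, an estimate at half the week-4 effect implies (1/0.5)² = 4 times the patients. Baseline NRS, which is collected in everyone, is also given no role in reducing variance.

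**Working it through.** **The plan's own figure.** Section 2.7.1 sets 20 patients (10 per group) on feasibility and gives no effect size, SD or power. There is nothing to reproduce.

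**What the group term estimates.** Let δ_t be the group difference at visit t. With balanced data, random subjects and fixed effects for group and visit only, the group coefficient is

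(1/K) × Σ δ_t over the K modelled visits.

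Carrying the last observation forward fills later gaps, so the visits get equal weight. In 200 simulated trials (10 per arm; weeks 0, 2, 4 and 8) the fitted coefficient equalled this simple mean each time, with a largest gap of about 1e-14.

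**Share of the week-4 effect recovered.** The trajectories are assumptions, because the article gives none. The week-4 effect is set to 1, week 2 to 0.5 and baseline to 0.

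| Kept at week 8 | Weeks 0, 2, 4, 8 | Weeks 2, 4, 8 only |
|---|---|---|
| none | (0 + 0.5 + 1 + 0)/4 = 37.5% | (0.5 + 1 + 0)/3 = 50% |
| half | (0 + 0.5 + 1 + 0.5)/4 = 50% | (0.5 + 1 + 0.5)/3 = 67% |
| all | (0 + 0.5 + 1 + 1)/4 = 62.5% | (0.5 + 1 + 1)/3 = 83% |

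The ceiling with baseline included is (0 + 1 + 1 + 1)/4 = 75%, reached if the effect is complete by week 2 and fully kept at week 8.

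On the five visits of Table 2, with a quarter of the effect assumed at week 1, the share is (0 + 0.25 + 0.5 + 1 + 0)/5 = 35% to (0 + 0.25 + 0.5 + 1 + 1)/5 = 55%. If week 1 is also pre-dose and the effect is lost by week 8, it is (0 + 0 + 0.5 + 1 + 0)/5 = 30%.

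**Power.** Assumptions: week-4 effect 1.3 SD, equal variances, equal correlation ρ = 0.5 between visits, half/full/half profile, 10 per arm, two-sided 5%, noncentral t.

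1. Stated main effect, four visits: effect 1.3 × 0.50 = 0.65 SD. SE = √[(2/10)(1 + 3ρ)/4] = √(0.2 × 0.625) = 0.354 SD, 18 df. Power is about 41%.
2. Same model without baseline as a response: effect 1.3 × 0.667 = 0.867 SD. SE = √[(2/10)(1 + 2ρ)/3] = √(0.2 × 0.667) = 0.365 SD, 18 df. Power is about 61%.
3. The same three-visit average, adjusted for baseline: SE = √{(2/10)[(1 + 2ρ)/3 − ρ²]} = √(0.2 × 0.417) = 0.289 SD, 17 df. Power is about 81%.
4. Week-4 contrast, adjusted for baseline: effect 1.3 SD. SE = √[(2/10)(1 − ρ²)] = √(0.2 × 0.75) = 0.387 SD, 17 df. Power is about 89%.

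For ρ = 0.3, steps 1 and 4 give about 51% and 82%; for ρ = 0.7, about 35% and 97%.

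**Where the gap comes from.** Dropping baseline as a response takes power from 41% to 61%, and using it as a covariate from 61% to 81%. Moving to week 4 takes it from 81% to 89%. That last step depends on persistence. The baseline-adjusted average has about 94% power if the effect is fully kept at week 8, more than the week-4 contrast, and about 56% if it is gone.

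**The case against.** The article gives the model one sentence, and section 2.9 shows that a full protocol (version 1.3) exists. Interaction terms and baseline handling are often left to such a document, and the sentence does not say that the terms are main effects only. That lowers confidence. It does not remove the point, because the article gives a list of factors with their roles, and fitting that list produces the averaged quantity.

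A reader might infer more than the documents support:

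- **That the model certainly averages in baseline.** Section 2.5.1 says when NRS is measured. Section 2.7.2 does not say which visits enter, or whether the response is the raw score or a change. Baseline as a response is the natural reading, but still an inference.
- **That the trial will report half the true effect.** That is one assumed trajectory among several. Week 4 as the target is also inferred from the end of dosing, since no primary visit is named.
- **That week 8 always dilutes.** It does so only as far as the effect fades off drug.
- **That the missing interaction alone costs 41% against 89% power.** Most of that gap comes from how baseline is handled.
- **That equal correlation is safe.** Eligibility keeps screening NRS at 3 or more and below 7. This tends to shrink the baseline SD and its correlation with week 4, so the 97% at ρ = 0.7 is probably optimistic.

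Power is also not the design criterion of a feasibility pilot with no stated hypothesis, and NRS will be collected visit by visit, so a week-4 difference can still be computed. These points stand, and they limit the severity.

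**Conclusion.** The point holds in a limited form. As written, the model's single treatment parameter is a group difference averaged over visits.

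If baseline is a response, that average is at most 75% of the week-4 effect, given an effect at weeks 2 and 8 no larger than at week 4. It is 37.5% to 62.5% under the assumed half effect at week 2. If baseline is not a response, the share is 50% to 83% under the same trajectories. The power figures of 41%, 61% and 89% illustrate one set of assumed values and are not properties of the trial.

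This should be fixed, but it does not invalidate the study. A reader might take it as fatal to the primary analysis; in an exploratory pilot the harm is mainly a diluted estimate carried into the planning of the larger trial.

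**What to change.** Replace the model sentence in section 2.7.2 with a repeated-measures model for post-baseline NRS, with baseline NRS as covariate and group, visit and group-by-visit as fixed effects. Name the adjusted between-group difference at week 4 (end of treatment), with its 95% CI, as the main estimate. Report the other visits, including week 8, separately.

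First reconcile sections 2.5.1, 2.5.2.1 and 2.5.2.2, where visit 1 is baseline, with Table 2, where visit 1 is week 1 and DLQI and ESS have no week-0 entry. The answer decides which values are pre-dose and whether a week-1 NRS belongs in the model. Use the same model for DLQI and ESS only if a pre-dose value exists for them.

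The cost is a paragraph of text, one or two degrees of freedom, and no new NRS data.

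### The stated efficacy model implies equal variance at every visit; if the entry-restricted baseline NRS is one of those visits, week-specific tests can be mildly anti-conservative

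*Protocol article*

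**What the plan says.** Section 2.7.2 states that for efficacy "the mixed-effect model for repeated measures will be used", "with each group and visit time as fixed factors and subjects as random factors". It names no residual covariance structure, no group-by-visit interaction and no baseline covariate, and does not say whether the response is the raw score or its change. Tests are "two-sided and set at 5% level of significance".

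Table 1 bounds the entry score on both sides: inclusion requires "NRS score of ≥ 3 for upper body pruritus" and exclusion applies at "NRS score of ≥ 7 for upper body pruritus". After entry the scale is unrestricted: "The NRS is a numerical rating scale anchored at 0 and 10".

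On timing, Section 2.5.1 says "The measurement will be performed at baseline (visit 1), 2 weeks, and 4 weeks during and after treatment", followed by the follow-up visit, so the text gives four NRS time points, with baseline counted among the visits. Table 2 labels the screening column as week 0 baseline and also schedules NRS at week 1, which makes five.

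**The concern.** With independent residuals, a random subject effect is compound symmetry: the same variance at each visit and the same correlation between any two. The entry window narrows the spread of NRS at baseline only. If baseline is a response visit, its small variance is pooled into the error used at later visits, and differences at those visits look more precise than they are. So the doubt about equal variance comes from this trial's own entry criteria and is not a general preference for a richer covariance.

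There are two practical consequences. A week-4 or week-8 comparison between groups could be declared significant at 5% too often. And if the pooled variance were used to plan the larger trial that the Discussion has in view, it would understate the variability of the follow-up score.

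**Working it through.** The article gives no SD for NRS at any visit, and the sample size of 20 rests on feasibility, so there is no planned figure to reproduce. The follow-up SDs and correlations below are assumptions.

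**Inputs.** 10 per group (Section 2.7.1); two-sided 5% (Section 2.7.2); baseline scores 3, 4, 5 or 6 (Table 1, whole numbers).

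**Baseline variance.** If the four values are equally likely, the mean is 4.5 and the variance is (2.25 + 0.25 + 0.25 + 2.25)/4 = 1.25, so the SD is 1.12. The largest possible SD, with half at 3 and half at 6, is 1.5.

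**Standard errors.** With complete data and a group-by-visit term, the true SE of a group difference at a visit with variance v is √(2v/10). The compound-symmetry SE is √(2·v̄/10), where v̄ is the mean of the visit variances. Their ratio is √(v̄/v). With four visits and a common follow-up SD s, v̄ = (1.25 + 3s²)/4; with five visits, v̄ = (1.25 + 4s²)/5.

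For s = 2 and four visits, v̄ = (1.25 + 12)/4 = 3.31. The model SE is √(2 × 3.31/10) = 0.814 and the true SE is √(2 × 4/10) = 0.894, a ratio of 0.910.

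| Follow-up SD | SE ratio, 4 visits | SE ratio, 5 visits | Rejection, week-4 difference | Rejection, week-4 change |
|---|---|---|---|---|
| 1.12 | 1.000 | 1.000 | 5.0% | 4.9% |
| 1.5 | 0.943 | 0.955 | 6.6% | 4.0% |
| 2.0 | 0.910 | 0.929 | 7.5% | 3.5% |
| 2.5 | 0.894 | 0.917 | 8.0% | 3.5% |

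The rejection rates are simulated with no drug effect, four visits, correlation 0.5, 10,000 runs and Satterthwaite degrees of freedom. The Monte Carlo SE is √(0.05 × 0.95/10,000), about 0.2 points. A separate simulation over correlations 0.3–0.5 gave 6.1–7.9% for the week-4 difference and 2.8–4.1% for the week-4 change.

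**Rising SDs (1.12, 1.4, 2.0, 2.3).** The difference test rejects 8.3% of the time at week 4 and 12.7% at week 8. The change-from-baseline test rejects 4.0% at week 4 but 6.9% at week 8.

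**Baseline not a response row.** With equal follow-up SDs the ratio is 1.000 and there is no error. With follow-up SDs of 1.4, 2.0 and 2.3 the week-8 ratio is still 0.842, so removing baseline does not by itself settle the variance question.

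**Additive model exactly as written.** The group main effect compares subject means. Over the same SD patterns, with correlations 0.3 and 0.5 and 20,000 runs, it rejected 4.5–5.3% of the time. If baseline is a response row and the drug effect is a constant d afterwards, this test estimates (0 + d + d + d)/4 = 0.75d with four visits, or 0.80d with five if the drug acts at all four later ones.

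**Visit-specific variances.** Rejection was 4.7–5.4% in every scenario, for both differences and changes. With baseline NRS as covariate the week-4 test held 4.9–5.3%.

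**The case against.** The strongest reply is that the plan is being read selectively. Taking silence on residual covariance to mean independent residuals, while adding a group-by-visit term that is equally unstated, produces the inflation in a model the article does not describe. A model of this class can carry a residual structure with unequal variances, and a condensed article commonly leaves that to the analysis plan, which is not shown. Section 2.7.2 does not say that baseline is a response row. Read literally throughout, the additive model has a group test that is valid whatever the visit variances, given complete data.

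Much of this stands. A reader might infer that the visit-specific error bars in this trial are wrong; the documents do not support that. It needs three things the article does not state: baseline as a response, an interaction, and larger variance later. Nor can one say that change-from-baseline tests are always conservative, since the rising-SD case goes the other way at week 8.

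What survives is that the article does more than stay silent. It names the within-subject term and the fixed factors, and Section 2.5.1 lists baseline as a visit of the primary outcome, so baseline as a level of visit time is the natural reading. On that reading the additive test keeps its level but dilutes the effect, while adding the interaction makes the variance assumption matter.

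**Conclusion.** The point holds conditionally. The model as written implies a common variance and correlation across visits, which is doubtful under the 3–6 entry window. With baseline as a response row, a group-by-visit term, four visits and follow-up SDs of 1.5–2.5, week-specific standard errors are about 6–11% too small and a 5% test rejects about 6–8% of the time. With the week-1 score of Table 2 as a fifth visit, the shortfall is about 5–8%. Week-4 change contrasts are then conservative, at about 3–4%; that direction does not carry over to every visit.

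The result also assumes that the baseline score analysed is the one on which entry is judged, as the week-0 column of Table 2 suggests; Section 2.5.1 calls baseline visit 1, and the two should be reconciled. If later SDs equal the baseline SD, there is no error.

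If the pooled variance were carried into planning at follow-up SD 2, it would be 3.31 instead of 4, or 17% too low. Because the trial is an exploratory pilot, priority is low to moderate.

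**What to change.** Replace the model sentence in Section 2.7.2 with a specification on these lines:

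> NRS at the post-baseline visits will be the response, with group, visit and group-by-visit as fixed effects and baseline NRS as a covariate. Within-subject covariance will be unstructured, with Kenward-Roger degrees of freedom and no random subject term. If the model does not converge, heterogeneous compound symmetry will be used.

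State which NRS assessment is baseline, and bring Section 2.5.1 and Table 2 into agreement on whether week 1 is a visit of the primary outcome. With weeks 2, 4 and 8 the unstructured matrix has 3 variances and 3 covariances, 6 parameters; a fourth post-baseline visit makes it 4 + 6 = 10.

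The cost is a few lines of SAS code and no new data, since baseline NRS is already collected. The downside is slightly fewer error degrees of freedom and, with 20 participants, a real chance of needing the fallback, which is why it should be fixed in advance.
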